### Statistical analysis

#### Descriptive statistics

Descriptive statistics (means ± SDs or frequencies) will be used to summarise the patient characteristics, including age, sex, years of formal education, time since AD diagnosis, marital status, living location (urban or rural), number of children, baseline MMSE score, baseline ADL score, number of comorbidities, number of caregivers, and information about the caregivers (such as sex, age, relationship to patient, and employment status). Mean values and ranges will be also presented because cost data are commonly positively skewed and the median cost could be zero for highly skewed data.

#### Calculation of costs due to AD

Different distributions will be considered for the monetary costs associated with AD, including normal, lognormal, exponential, and gamma. To compare the costs of different subgroups, *t*-tests or Kruskal-Wallis analysis of variance will be used. For base case analyses, GLMs will be developed using the gamma distribution with a log-link function [35]. Models will be developed with the total cost per person per year as the dependent variable, and independent variables will be selected using a backward selection method (*P* > 0.05 for removal), with patient age, patient sex, and MMSE severity all forced to remain in the model. Considering the diverse of research centres sites, we also added the sites as a covariant in the analysis. The variables used for backward selection will be years of formal education, time since AD diagnosis, marital status, location of residence (urban or rural), number of children, baseline MMSE score, baseline ADL score, the number of caregivers, the number of comorbidities, and caregiver demographics.

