### Measures

#### Total cost per patient per year

The total cost per patient per year is determined by adding the annual direct medical costs, direct non-medical costs, and indirect costs for each patient. When calculating the cost of the recuperation fee for patients who required nursing care in nursing homes, gerocomiums, or care facilities, 8% of the basic cost is subtracted to reflect the AD patient’s basic cost of living [30]. Two approaches are being used to estimate the monetary loss of informal caregivers. For the informal caregivers who have no stable job before taking care of the AD patients, the average labour market income reported by each research centre is being multiplied by the amount of time spent being a caregiver to obtain the monetary loss. For individuals with a stable job before taking care of the AD patient, the monetary loss is being obtained by multiplying the hourly salary before they stop working by the time spent (hours) being a caregiver. All of the costs will be converted into the average annual cost.

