#### Per capita annual cost of AD patients (who accepted or did not accept treatment)

The cost associated with treating dementia patients (F_1_) is divided into two groups: “outpatient costs” and “hospitalised or inpatient costs.” F_1_1_ is defined as the average annual cost in the inpatient group (average annual cost × the number of inpatients annually), and F_1_2_ is the average annual cost in the outpatient group (average annual cost × the number of outpatients annually). Patients described as not accepting treatment are those who did not select either “outpatient service costs” or “hospitalised costs” in their questionnaire. F_2_ is defined as the average annual cost per AD patient who did not accept treatment.

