#### Nationwide cost due to AD

A pilot study is performed, which reveal that the average annual ratio of inpatients to outpatients in different hospitals is ~1:6. Hence, the number of patients who undergo treatment nationwide (M_1_) is multiplied by 1/7 or 6/7 to obtain the number of hospitalised patients with AD (M_1_1_) and the number of outpatients with AD (M_1_2_), respectively. Thus, the total national annual cost of patients who accept treatment is M_1_1_ × F_1_1_ + M_1_2_ × F_1_2_. M_2_ is defined as the number of patients who did not accept treatment, and this value is multiplied by F_2_ to obtain the total annual national cost of patients who do not accept treatment. Therefore, the total annual national cost of patients with AD is M_1_1_ x F_1_1_ + M_1_2_ x F_1_2_ + M_2_ x F_2_. To estimate the costs attributable to AD, generalised linear models (GLMs) related to coexisting conditions (stroke, diabetes, heart disease, hypertension, lung disease, cancer, arthritis, and psychiatric problems) and demographics (sex, age, educational level, marital status, and household income) are used. Moreover, we estimate the total numbers of people who will be living with AD in 2020, 2030, 2040, and 2050 to predict the total annual cost of AD in future decades. Few large-scale national surveys of the monetary cost or economic burden of AD have been conducted in China, or indeed in Asia. To remedy this lack of data, we also systematically review COI studies of AD that report annual costs per patient. This will enable estimation of the proportion of the global burden of AD costs faced by China. Furthermore, it will enable comparison of the economic burden of AD in developed and developing countries.

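### Kruskal-Wallis, the only test named for comparing costs across three or more subgroups at once, compares ranks, while the study's cost quantities are means

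*Protocol article*

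**What the plan says.** The subgroup method is one sentence in the Protocol article, Calculation of costs due to AD. Its purpose is given as "To compare the costs of different subgroups", and the tools are t-tests or a rank test: "Kruskal-Wallis analysis of variance will be used".

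The other cost quantities in the article are averages:

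- **Sample size** fixes the precision of an average annual cost, from an SD of 11,037 and an allowable error of 500.
- **Total cost per patient per year** ends with "All of the costs will be converted into the average annual cost".
- **Per capita annual cost of AD patients** defines its inputs as "the average annual cost in the inpatient group", the matching outpatient quantity, and "the average annual cost per AD patient who did not accept treatment".
- **Nationwide cost due to AD** multiplies these by patient counts: "the total annual national cost of patients with AD is M_1_1_ x F_1_1_ + M_1_2_ x F_1_2_ + M_2_ x F_2".
- **Calculation of costs due to AD** takes a gamma GLM with log link as the base case, which is a model for mean cost.

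On the expected shape of the data, Descriptive statistics says that "cost data are commonly positively skewed and the median cost could be zero for highly skewed data".

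**The concern.** Kruskal-Wallis asks whether values in one group tend to rank above those in another. That coincides with a question about means only when the group distributions have the same shape. With skewed costs, a group with a few very expensive patients can have a high mean and middling ranks. A group with many zero-cost patients can have low ranks and an ordinary mean.

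The t-test does compare means, but only for two groups at a time. Severity has three levels in Criteria for AD patients, and there are several types of care site. For one overall comparison of such groups, the rank test is the only one named. The Results section says that subgroup costs will be reported. A p-value beside a set of mean costs would naturally be read as a statement about those means, and it may not be one.

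**Working it through.** **1. The plan's own figure.** The sample size formula is n = (z × S / δ)². Alpha is not stated; two-sided 0.05 is assumed. Then n = (1.96 × 11,037 / 500)² = 1,871.9, rounded up to 1,872, as stated. Allowing for 25% loss, 1,872 / 0.75 = 2,496, or about 2,500. The figure reproduces, and it is the precision of a mean.

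**2. Inputs for the check.** The article gives no subgroup distributions or subgroup sizes. All distributions below, and group sizes of 100 to 900, are assumptions, with a 5% test level throughout. With two groups, Kruskal-Wallis is equivalent to the two-sided Wilcoxon rank-sum test.

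**3. Formula for lognormal costs.** Take log-SDs s₁ and s₂ and a common mean m. The log-scale means are log m − s²/2, so they differ by (s₁² − s₂²)/2. The probability that a random patient of the less variable group costs more than one of the other group is

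P = Φ( [(s₁² − s₂²)/2] / √(s₁² + s₂²) ).

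With n per group, the null standard error of the estimate of P is √((2n + 1)/(12n²)): 0.0409 at n = 100 and 0.0167 at n = 600. The rejection rate is roughly Φ(|P − 0.5|/SE − 1.96).

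- *Log-SD 1.0 vs 0.6:* P = Φ(0.32/1.166) = Φ(0.274) = 0.608. At 100: 0.108/0.0409 = 2.64, giving 75%. At 600: 6.48, giving 100%.
- *Log-SD 1.0 vs 0.8:* P = Φ(0.18/1.281) = Φ(0.141) = 0.556. At 100: 1.37, giving 28%. At 600: 3.35, giving 92%.
- *Equal medians, log-SD 1.0 vs 0.6:* the log-scale means are equal, so P = 0.5 and rejection stays near 5% at any n. The means differ by the factor exp((1.00 − 0.36)/2) = exp(0.32) = 1.38.

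**4. Simulation of the same cases** (2,000 runs each), with the unequal-variance (Welch) t-test as the comparison of means:

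| Case | n per group | Kruskal-Wallis | Welch |
|---|---|---|---|
| Equal means, 1.0 vs 0.6 | 100 | 76% | 7% |
| | 600 | 100% | 5% |
| Equal means, 1.0 vs 0.8 | 100 | 27% | 5% |
| | 600 | 92% | 5% |
| Equal medians, means 38% apart | 100 | 6% | 53% |
| | 600 | 4% | 100% |

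Another run of the 1.0 vs 0.8 case at 100 per group gave 29%, so about 28% is a fair summary.

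**5. Other assumed shapes, 300 per group.**

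- Equal means, gamma shape 2 vs 0.8: Kruskal-Wallis 90%, Welch 5%.
- Equal means, no zeros vs 40% zeros: 100% vs 3%.
- Lognormal means of 10,000 (log-SD 0.6) and 11,500 (log-SD 1.0): Kruskal-Wallis rejects in 73% of runs, each time ranking the group with the lower mean higher.

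**6. The benign case.** With a common gamma shape (shape 1) and equal means, the distributions are identical and Kruskal-Wallis rejected in 4 to 5% of runs. With the same shape and means 20% apart, it rejected in 50% of runs at 300 per group against 62% for Welch, both in the right direction. At 900 per group the rates were 92% and 98%.

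**The case against.** The case on the other side is substantial:

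- **The main results do not use this test.** The per-patient cost, the national total and the gamma model all work on means. This stands. A reader might infer that the headline cost figures are at risk; the document does not support that.
- **Much of the mean-based comparison is already planned.** The base-case model forces in MMSE severity, adds site, and has urban or rural residence as a candidate variable. This stands for adjusted comparisons of those factors. It does not cover the unadjusted comparisons, for which the t-test or rank test is named.
- **A t-test is also named, and the rule for choosing may sit in an analysis plan that is not shown.** A missing rule is no finding here. But no such rule would make the t-test a single comparison of three or more groups, so the named method still has a target other than the mean.
- **Descriptive statistics does not make the mean the sole target.** It says "Mean values and ranges will be also presented because cost data are commonly positively skewed", which is a statement about reporting. A reader might take it as the plan's choice of estimand; it does not go that far. The commitment to means rests on the sample size, the cost definitions, the national total and the GLM.
- **Rejecting because distributions differ is a correct answer to the question Kruskal-Wallis asks.** This stands. It becomes an error only if reported as a difference in mean cost, and the article does not say that it will be.
- **The illustrations are constructed.** This also stands. A gamma model with common dispersion gives all groups the same shape, and there the rank test behaves well. A reader might infer that the subgroup conclusions will be wrong; the document gives no subgroup distributions from which to show that.

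**Conclusion.** The point holds within limits. The article names, for cost comparisons across three or more subgroups, a test whose target differs from the mean costs on which the rest of the plan is built. If subgroups differ in spread, shape or share of zeros, the p-value can signal a difference where means are equal, miss one where means differ, or favour the group with the lower mean. The skew and possible zero median that the article itself expects make such differences plausible, but it does not show them.

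The size depends on the assumed distributions and group sizes. At equal means, rejection ranged from about 28% (mild difference in spread, 100 per group) to 100%. It was about 5% when medians were equal and means 38% apart, and at its nominal level when equal-mean groups shared a shape. The effect is confined to unadjusted subgroup comparisons. The change is worth making before those are reported, but it is not a threat to the study's main findings.

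**What to change.** Base unadjusted subgroup comparisons of cost on means. The most direct route is the log-link GLM already planned, with the subgroup as the only covariate. It handles any number of groups and gives an overall test; a Welch test or a bootstrap would also serve. Use standard errors that respect site, for example clustered by site or from a bootstrap over sites. Report mean differences or ratios with intervals.

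Kruskal-Wallis can stay as a descriptive comparison of distributions, labelled as such, and should not support statements about mean cost.

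The cost is a little extra analysis and no new data. Intervals for small, heavily skewed subgroups will be wider, which reflects how much those data say about a mean.

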#### Others

To understand the relationship between AD costs and other factors, parameters such as social demographics and disease details are also investigated. The social demographics include sex, age, education level, marital status, occupation, salary, and the number of children. The disease details include age at onset of AD, clinical evaluations (based on ADL, GDS, MMSE and neuropsychiatric inventory [NPI] [29]), and comorbidities (e.g., stroke, diabetes, heart disease, hypertension, hyperlipidemia, lung diseases, cancer, arthritis, and other diseases of the nervous system).

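### Backward selection at P > 0.05 in the base-case cost model distorts weak covariate effects and makes the reduced model's P-values and intervals invalid, although the sample can carry the full model

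*Protocol article*

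**What the plan says.** The rule is in the protocol article, Statistical analysis, under Calculation of costs due to AD. The base case is a gamma model with log link ("GLMs will be developed using the gamma distribution with a log-link function") for total cost per person per year. In it, "independent variables will be selected using a backward selection method (*P* > 0.05 for removal"). Three covariates are exempt from that rule: "with patient age, patient sex, and MMSE severity all forced to remain in the model". Site is included as well: "we also added the sites as a covariant in the analysis".

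The removable variables come in one list. Its first part reads "The variables used for backward selection will be years of formal education, time since AD diagnosis, marital status, location of residence (urban or rural"). The rest of the list reads "number of children, baseline MMSE score, baseline ADL score, the number of caregivers, the number of comorbidities, and caregiver demographics". Caregiver demographics are not itemised there, but Descriptive statistics gives examples: "information about the caregivers (such as sex, age, relationship to patient, and employment status").

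The section headed Others explains why these variables are collected: "To understand the relationship between AD costs and other factors, parameters such as social demographics and disease details are also investigated". Nationwide cost due to AD says that models with coexisting conditions and demographics, among them educational level and marital status, are used to estimate the cost attributable to AD. None of the planned sensitivity analyses varies the covariate selection.

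**The concern.** The article fixes this rule itself, so the point does not rest on detail that a fuller analysis plan might supply.

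Three things follow from the rule:

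- **Estimates.** A covariate stays only if its estimate is large relative to its standard error. A weak true effect is therefore either dropped, and easily read as no relationship, or kept in the samples where chance made it look large.
- **Inference.** Standard errors, P-values and intervals from the final model are computed as if that model had been chosen in advance.
- **Adjustment.** Education, marital status and number of comorbidities can all be removed. These are the kinds of adjustment that Nationwide cost due to AD says are used for AD-attributable cost. The article does not say whether the two sections describe one model. If they do, a promised adjustment can disappear because a P-value was 0.06.

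At stake are the statements about which factors go with higher cost, and the adjusted costs from this model. Multiplicity over the candidates is a second, separate problem.

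**Working it through.** **Reproducing the plan's own figure.** Inputs from Sample size: SD 11,037, allowable error 500, two-sided alpha 0.05 (assumed). n = (1.96 × 11,037 / 500)² = 1,871.8, so 1,872; and 1,872 / 0.75 = 2,496, matching the planned 2,500 or so. The sample size reproduces, and 1,872 is the number to use for the analysis.

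**Candidates.** Nine named variables (education, time since diagnosis, marital status, residence, children, MMSE score, ADL score, caregivers, comorbidities) plus a caregiver block of one to four items: 10 to 13.

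**Why weak effects are inflated.** In a gamma log-link model, the standard error of a coefficient per SD of an uncorrelated covariate is about CV/√n. The document gives no residual CV, so 1.0 and 1.5 are assumptions.

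- CV 1.0: 1/√1,872 = 0.0231. To stay in, an estimate must exceed about 1.96 × 0.0231 = 0.045.
- CV 1.5: 1.5/√1,872 = 0.0347, so the bar is about 0.068.

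A true effect of 0.04 cannot be retained at its true value in either case.

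**Simulated backward elimination.** Settings: n = 1,872, 13 candidates (six true effects, seven null), pairwise correlation 0.2, no site term, 400 runs. Effect sizes are assumed.

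| True effect per SD | Kept, CV 1.0 | Mean when kept | Kept, CV 1.5 | Mean when kept |
|---|---|---|---|---|
| 0.04 | 41% | 0.068 | 21% | 0.096 |
| 0.06 | 70% | 0.074 | 44% | 0.102 |
| 0.08 | 91% | 0.086 | 63% | 0.109 |
| 0.10 | 98% | 0.105 | 80% | 0.120 |
| 0.15 | 100% | 0.154 | 99% | 0.159 |

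At 0.04 and CV 1.0 the overstatement is 0.068/0.04 = 1.7 times; another simulation with 12 candidates gave 0.063, or 1.6 times. At 0.10 it is about 5% (CV 1.0) or 20% (CV 1.5). At 0.15 it is 3% or 6%. The full model gave a mean of 0.041 for a true 0.04 at CV 1.0, so it is essentially unbiased.

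**Multiplicity.** For k independent null candidates, the chance of at least one P ≤ 0.05 is 1 − 0.95^k:

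- k = 5: 22.6%
- k = 7: 30.2%
- k = 10: 40.1%
- k = 13: 48.7%

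Simulated backward elimination with all candidates null gave 40–43% (k = 10) and 44–49% (k = 13). With seven null and six real effects, simulations gave 35–40%. Direct comparisons with the unselected full model gave 48% against 48% (13 null), and 40% with selection against 36% without (seven null). Selection changes this rate little. A 60-run check with 81 site dummies gave 58%, with a standard error of about 6 points, which is too imprecise to build on.

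**Can the sample carry the full model?** If each of the 81 centres is a level, there are about 93 to 99 parameters: 1,872/93 = 20.1 and 1,872/99 = 18.9 patients per parameter. With a coarse site-type term (about 18 parameters) it is 1,872/18 = 104.

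**The case against.** A reader might infer that backward selection makes a spurious cost driver about as likely as not. The documents do not support that. The 40 to 49% requires every candidate to be unrelated to cost, which is implausible here: caregiver time and comorbidity treatment are costed into the outcome itself, so caregiver numbers and comorbidities should matter. The rate is also that of any 10 to 13 unadjusted tests, and the full model would show much the same. This objection stands, and multiplicity is kept separate for that reason.

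A reader might also infer that all retained effects are overstated. They are not: at CV 1 the inflation is 5% or less from 0.10 per SD upwards.

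Nor do the documents support a claim that the headline result is wrong. The main findings are the per-patient and national annual costs, and the national total multiplies patient numbers by group average costs without using the selected covariates. The article nowhere promises a confirmatory list of drivers, and age, sex and MMSE severity are protected from removal.

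Finally, putting every listed variable in is not free of problems. MMSE severity is graded from the MMSE score, so the two overlap, and residence overlaps with site. This also stands and shapes the fix.

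The objections leave the selection rule itself undefended: it gives invalid intervals, distorts weak effects and lets adjustment variables fall out, with no need for it at this sample size.

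**Conclusion.** The point holds in a limited form. Backward elimination at P > 0.05 biases weak covariate effects away from zero when they are kept (0.04 reported as about 0.06 to 0.07 at CV 1), hides them otherwise, and yields P-values and intervals that ignore the selection. Strong effects are little affected at CV 1; at CV 1.5 an effect of 0.10 is about 20% too large. It also allows removal of education, marital status and comorbidity count from the adjusted cost model.

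The chance of at least one false association, 40 to 49% if all candidates are null and roughly 23 to 40% if five to seven are, belongs to unadjusted testing and not to the selection step.

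The harm falls on covariate associations and adjusted costs, not on the national total. The sizes rest on assumed CVs, effect sizes and correlations, none of which the article gives. The change is worth making because the better analysis is simpler and the data can support it.

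**What to change.** In Calculation of costs due to AD:

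1. Replace the backward-selection rule with a full pre-specified base-case model: age, sex, site, the listed candidates, and one MMSE term only. Severity is already forced in, so the score from which it is graded should leave the list.
2. Itemise the caregiver variables, and check that residence can be estimated alongside site.
3. Report every estimate with its 95% interval, whatever its P-value.
4. Label the factor associations and the subgroup comparisons as exploratory. This step addresses the multiplicity; the full model alone does not.
5. Keep the backward-selected model as a sensitivity analysis.
6. State whether this is the model that Nationwide cost due to AD uses for attributable cost, and if so align the adjustment variables.

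No new data are needed. The cost is slightly wider intervals, a longer table, and the short check on overlapping terms. Even with 81 site dummies, about 19 to 20 patients per parameter remain at 1,872.

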#### Sensitivity analyses

Sensitivity analyses will be conducted to examine the robustness of the results from the base case model and explore correlations between certain factors that could impact each other. First, the total costs of dementia will be estimated using the prevalence rates derived from a systematic review. Then the minimum and maximum salaries (rather than the average) will be used to estimate the relative costs. The total costs will be estimated by assuming that 70 and 99% of patients with AD are living at home, instead of 86% in the primary option. Furthermore, different costing caregiver time will be used to estimate the total cost. All of the analyses will be performed using R software version 3.2.3.

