### Sample size

The sample size was calculated using the equation, $$ n=\frac{U_{1-\alpha /2}^2{S}^2}{\delta^2} $$ where *S* was the stand division and *δ* was the allowable error. The planned sample size was generated based on previous data obtained from an economic evaluation of an AD-type dementia study [26]. Based on the standard deviation (SD) of AD-related costs per patient per year (11,037) and an allowable error of 500, the total sample size required was 1,872. Therefore, the planned total sample size in this study was ~2,500 to allow for a defective rate of 25%. Before starting the study, information was surveyed from all randomly selected participating sites, including the number of dementia physicians at each site, the number of AD patients, and the proportion of outpatients and inpatients in the last year. Based on these data 20–40 patients with AD will be assigned for each site. The sites include hospitals (Tier 3 hospitals, gerontology hospitals, mental health centres and psychiatric hospitals), nursing homes, gerocomiums, care facilities, and residences.

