#### Current total number of patients with AD in China

A model is established to estimate the total number of Chinese patients with AD in 2015 based on the literature. The total number of patients with AD is defined as M and the percentage of AD patients who received anti-dementia treatment is defined as d%. Therefore, the number of anti-dementia treated patients (M_1_) is M × d%, and the number of patients not treated for dementia (M_2_) is M × (1–d)%. Based on previous reports, the percentage of AD patients who are treated for dementia is 10–30% [31, 32]. Epidemiological studies have revealed that the number of AD patients in China aged ≥ 60 years in 1990, 2000, and 2010 was 1.93 million, 3.71 million, and 5.69 million, respectively [8, 33, 34]. A linear regression model is used to estimate the age-specific prevalence of AD in 2015 by recording the prevalence of AD among different-aged patients. By multiplying the percentage of AD among elderly individuals aged ≥ 60 years by the total national elderly population (aged ≥ 60 years) in 2015, we obtain the estimated total number of AD patients of China, which is defined as M.

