We carefully consider cost classifications for the total cost of AD. Cost in the present study includes direct medical costs, direct non-medical costs, and indirect costs. The cost classification used was in accordance with those that are commonly used internationally [11, 38]. This strategy is intended not only to ensure that the results cover all aspects of costs for AD patients but also to enable comparison with findings from developed countries. In addition, the cost of AD includes both AD patients and their caregivers. Our previous study revealed that 84.9% of AD patients are cared for by non-professional caregivers at home [39]. This is because China faces a shortage of nursing homes, and the Chinese tradition of filial piety mandates that when they lose the ability to live independently, patients should be cared for by their families. Therefore, it is important to include caregivers in calculating AD costs. These procedures are conducted to ensure the accuracy, reliability, and credibility of data on AD in China.

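### The sensitivity analysis varies an 86% living-at-home share that the printed cost formula does not contain, so as written it cannot change the national total

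*Protocol article*

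**What the plan says.** The Sensitivity analyses section states that total costs will be re-estimated by "assuming that 70 and 99% of patients with AD are living at home, instead of 86% in the primary option". It thus attributes an 86% home share to the primary calculation.

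The primary calculation is set out under Measures. The number of patients, M, is split by the treated fraction d; the article reports from earlier work that "the percentage of AD patients who are treated for dementia is 10–30" per cent. The treated number "is multiplied by 1/7 or 6/7 to obtain the number of hospitalised patients with AD" and of outpatients respectively. Each group is multiplied by its average annual cost, so that "the total annual national cost of patients with AD is M_1_1_ x F_1_1_ + M_1_2_ x F_1_2_ + M_2_ x F_2". The section on per capita annual cost defines the three groups by service use: inpatient, outpatient, or neither reported in the questionnaire.

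Per-patient cost is the sum of each patient's direct medical, direct non-medical and indirect costs, converted to an annual average. Patients are enrolled from randomly selected hospitals, nursing homes and other care facilities, and residences. On numbers per site, the Sample size section says: "Based on these data 20–40 patients with AD will be assigned for each site".

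The nearest other figure is in the Discussion, which cites an earlier study by the same group: "84.9% of AD patients are cared for by non-professional caregivers at home".

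**The concern.** A sensitivity analysis replaces one input of the primary calculation and shows how far the answer moves. Here the input to be replaced is not in the calculation. An analyst who follows the article literally would either report three identical totals, which would look like robustness, or add an unplanned step to make the home share count.

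The home share is also a plausible driver of the result. Institutional patients generate formal care fees, from which 8% of the basic cost is deducted for ordinary living. Home patients mainly generate informal care, valued at wage rates. Because these are different cost streams, the residence mix inside each group average can move both headline results, the per-patient and the national annual cost. The plan to vary the share suggests that the investigators think it matters.

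**Working it through.** **The plan's own figure.** The 86% cannot be reproduced: no section derives it, sources it or enters it in a formula. The article's other arithmetic is not at issue. With two-sided alpha 0.05 assumed, 1.96² × 11,037² / 500² gives 1,872 after rounding up, and 1,872 / 0.75 = 2,496, or about 2,500. Over 81 centres, 2,500 / 81 = 30.9 patients each, inside the 20–40 range.

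**Step 1: does the printed total depend on the home share?** Let h be the share at home. Per patient, the printed formula is

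T/M = d × (F11/7 + 6 × F12/7) + (1 − d) × F2.

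The inputs are d (10–30%), the weights 1/7 and 6/7, and three group averages; h is not among them. With placeholder costs F11 = 3, F12 = 1.5 and F2 = 1 (assumed), the bracket is 12/7 = 1.7143. Then:

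- d = 10%: 0.1714 + 0.9 = 1.0714
- d = 20%: 0.3429 + 0.8 = 1.1429
- d = 30%: 0.5143 + 0.7 = 1.2143

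Each value is the same at h = 70%, 86% and 99%. The per capita section words F11 and F12 as average cost times number of patients, although the national formula multiplies by numbers again. I read them as per-patient averages; the result in this step does not depend on that reading.

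**Step 2: does the regression supply the missing term?** Under Calculation of costs due to AD, the gamma log-link model forces in age, sex and MMSE severity. The residence variable among the selection candidates is urban or rural, not home or institution. Site is a covariate, which adjusts for differences between centres but does not reweight the sample to a national home share. The model for attributable cost under Nationwide cost due to AD uses comorbidities and demographics, again without home or institution.

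**Step 3: what would the analysis show if the share did enter?** Set the mean cost at home to 1 and in an institution to r. The documents do not give r; I assume 0.5 to 3. The residence-weighted mean is h + (1 − h) × r.

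| r (assumed) | 86% home | 70% home (change) | 99% home (change) |
|---|---|---|---|
| 0.5 | 0.93 | 0.85 (−8.6%) | 0.995 (+7.0%) |
| 1 | 1.00 | 1.00 (0) | 1.00 (0) |
| 1.5 | 1.07 | 1.15 (+7.5%) | 1.005 (−6.1%) |
| 2 | 1.14 | 1.30 (+14.0%) | 1.01 (−11.4%) |
| 3 | 1.28 | 1.60 (+25.0%) | 1.02 (−20.3%) |

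These figures describe the per-patient mean. They carry over to the national total only if the same h and r hold among inpatients, outpatients and untreated patients, which nothing in the article supports.

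**Step 4: 86% against 84.9%.** At 84.9% the weighted mean is 0.849 + 0.151 × r. Against the 86% value, the change is 0.9245/0.93, or −0.6%, at r = 0.5 and 1.302/1.28, or +1.7%, at r = 3. The numerical gap is minor; what is missing is the source and definition.

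**The case against.** The strongest reply is that the article condenses a fuller plan. The reference to a primary option with 86% at home suggests that a home-share step exists somewhere, and an article need not print every step. This stands in part: the claim can be made only about the calculation as printed. It does not remove the contradiction, because the article writes that calculation out in full and then attributes to it an input it lacks.

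A reader might go further and infer that the headline mean is a plain average over a quota sample of care settings, biased by a calculable amount. The documents do not support this, for four reasons:

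- Sites were randomly selected. The 20–40 is a number per site, informed by a survey of each site's AD patients and its outpatient and inpatient proportions. No quota per care setting is stated.
- Recruitment site is not residence. Patients found through hospitals may live at home, so the mix of site types does not fix the home/institution split, and the text does not say how many of the 81 centres are nursing homes.
- The national total is weighted, by treatment and by inpatient or outpatient status. Only a residence weight is absent, and that is read from the lack of any statement.
- Institutional care cannot be presumed dearer than home care once informal care is valued at wages and 8% is deducted from institutional cost. The sign is open.

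Nor do 86% and 84.9% contradict each other. The first counts patients living at home; the second counts those looked after at home by non-professional caregivers. The article recognises paid care at home, so the first can exceed the second.

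**Conclusion.** The point holds as an inconsistency between two sections. The Sensitivity analyses section replaces a home share in the primary calculation, and the printed primary calculation has none. With the group averages held as estimated, the planned change to 70% or 99% moves the national total by exactly zero, whatever the true costs. Until a residence weight is stated, the mix inside F11, F12, F2 and the per-patient mean is the recruited one, not 86%.

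The consequence for the headline results cannot be sized from the documents. The range of about −9% to +25% at 70% home, and +7% to −20% at 99%, rests entirely on assumed cost ratios of 0.5 to 3. It shows that the check would be worth making properly, not that the estimate is biased by that much or in either direction. Confidence is high on the inconsistency and does not extend to any claim about bias.

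**What to change.** Make the formula and the sensitivity analysis agree:

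1. Classify each patient as living at home or in an institution by actual residence, not by recruiting site.
2. Compute the per-patient mean and F11, F12 and F2 separately for the two residence groups, and combine them with a stated national home share.
3. Give the source of the 86% and explain its relation to the 84.9%. Where shares specific to inpatients, outpatients and untreated patients are available, use them in place of one share for all.
4. Then vary the share to 70% and 99%.

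If no sourced share can be given, withdraw this sensitivity analysis and report costs by residence.

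The change is confined to the analysis, provided residence is recorded for patients recruited through hospitals. The price is a slightly larger variance from unequal weights. Splitting three averages by residence also makes six cells, of which some, such as institutional inpatients, may be small.
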